### Study conditions

*CBT-E*: a transdiagnostic 20-session version of CBT, CBT-E(nhanced). In this study we use the focused version for patients with a BMI above 17.5, designed to be suitable for the full range of ED diagnoses. CBT-E is a treatment for ED psychopathology, rather than for a specific ED diagnosis. The strategy underpinning CBT-E is to construct a transdiagnostic formulation (or set of hypotheses) of the processes that are maintaining the patient’s psychopathology and to use this formulation to identify the features that need to be targeted in treatment. This formulation is constructed at the beginning of treatment, but will be revised ,if needed, during therapy. In this way a tailor-made treatment is created.

Stage 1 (sessions 1–7) is an intensive initial stage, with appointments twice a week. The therapist and the patient together set up the formulation of the underlying maintaining factors, which will be used as a base for the remainder of the treatment. The aims of this stage are to engage the patient in treatment.

Stage 2 (sessions 8–9) are weekly appointments. This stage is a brief stage in which the therapist and patient take stock, review progress, identify any emerging barriers to change, modify the formulation and plan stage 3. This stage is important to identify problems with the therapy, to remove barriers and adjust treatment if needed. After stage 2 the treatment will become more personalized.

Stage 3, (sessions 10–17) is the main body of treatment. There are eight weekly appointments. The aim is to address the main mechanisms that are supposed to maintain the patient’s ED. How this is done precisely varies from patient to patient. The therapist can choose to pay attention to one or more defined maintaining factors.

Stage 4 (sessions 18–20) is the final stage of treatment and the focus shifts to the future. The appointments are scheduled at 2-week intervals. There are two aims: the first one is to ensure that the changes are maintained (over the subsequent 20 weeks until a review appointment is held), and the second one is to minimize the risk of relapse in the long-term.

After 20 weeks there is a review session. The most important aim in this session is to review what has been learned and achieved during treatment and what risk factors are to be taken into account when therapy has ended.

*TAU*: the usual treatment given at the participating treatment sites is in general based on CBT, individually or in a group with elements of existing CBT treatment protocols [26, 27]. Depending on the site’s treatment policy, this may vary from low-intensity care (weekly sessions) to high-intensity care. This high-intensity care consists of two group sessions a day for 2 days of the week, sometimes supplemented with individual sessions due to coexisting psychopathology. Most of the times more than one discipline (psychologist, dietitian, psychiatrist) is involved in applying the treatment. The type of treatment provided is registered.

### Selection and training of therapists

All CBT-E therapists are psychologists/psychiatrists or registered nurses/social workers (*n* = 10). All have at least 2 years of experience as a therapist in the field of EDs and have been working for at least 2 years according to CBT principles. All CBT-E therapists in the participating centers were trained as a group by [name] and had 20 supervision sessions through videoconferencing from [name]. A Dutch treatment manual was developed and will be used by all CBT-E participating therapists. All participating CBT-E therapists have treated at least three ED patients with CBT-E under supervision before entering the trial.

All TAU therapists are psychologists/psychiatrists or registered nurses/social workers who have at least 2 years of experience as therapists in the field of EDs. TAU did not include training or supervision of the therapists. TAU therapists have regularly standard, local collegial consultation.

The treatment integrity in CBT-E will be evaluated by recording all CBT-E sessions. Two audiotaped sessions of every CBT-E patient will be randomly selected (from, respectively, stages 1/2 and stages 3/4) and the use of specific therapeutic interventions according to the treatment manual will be scored on several 7-point Likert scales. The first 20 audiotapes will be double rated to assess interrater reliability. Evaluation of the CBT-E sessions will be executed by psychologists who are familiar with the treatment protocol (trained through the online training in CBT-E developed by [name]), by ticking on prearranged checklists whether all due aspects of specific therapy stages have been handled adequately by the therapist.

### Objectives

The primary objective of this study is to assess whether CBT-E is more optimal in terms of a higher percentage of recovery from EDs compared to TAU. The secondary objectives are to assess whether CBT-E is more effective in (1) reducing important aspects of ED psychopathology, (2) reducing indications for the presence of comorbid psychopathological conditions and additionally comorbid symptoms of anxiety and depression, (3) improving health-related quality of life and (4) effectuating a better cost-effectiveness, compared to TAU.

Moreover, self-esteem, perfectionism and interpersonal problems are repeatedly measured during this RCT to examine their possible predictive and mediating effects on treatment outcome.

### Measurements

#### Screening and primary treatment outcome

*Structured Clinical Interview for DSM Axis-I Disorders (SCID-I).* The SCID-I [29, 30] will be used to assess the presence of an ED. Only the section about EDs will be administered. Because the SCID-I only covers AN, BN, and EDNOS-BED, skip rules were changed or omitted and parts of the *Eating Disorder Examination (EDE)* [31] were added in order to diagnose DSM-5 AN, BN, BED and OSFED [32]. The interview will be used both to obtain a DSM-5 diagnosis for inclusion and as a treatment outcome measure at T2 (at the end of treatment, 20 weeks after treatment has started) and T4 (80 weeks after the start of treatment). Several studies found moderate to excellent interrater agreement for determining the presence of Axis-I disorders using the original SCID-I [33] and good test-retest reliability [34, 35].

#### Secondary study parameters

*The Eating Disorder Examination-Questionnaire (EDE-Q)* [36, 37]. This questionnaire is a self-report measure that was adapted from the interview-based EDE [38] and measures ED pathology. It consists of 36 items that are scored on a 7-point scale. The total score is used as an indicator for the level of ED pathology, with a higher score denoting more pathology. Good concurrent validity [39–42], discriminant validity [43] and acceptable criterion validity [42] have been demonstrated with adults. Moreover, the EDE-Q has been found to have good internal consistency and test-retest reliability in adults [44]. In studies comparing the EDE interview and EDE-Questionnaire the overall correlation coefficient ranged from .68 to .76. In general, participants obtain higher scores in the questionnaire than in the interview mode of administration [45, 46].

*Web Screening Questionnaire for common mental disorders (WSQ)* [47]. This self-report screening instrument will be used to screen for Axis-I disorders. It is a short screening instrument for depressive disorder, alcohol abuse/dependence, generalized anxiety disorder (GAD), post-traumatic stress disorder (PTSD), social phobia, panic disorder, agoraphobia, specific phobia, and obsessive compulsive disorder (OCD). The questionnaire consists of 15 questions. The sensitivity of the WSQ is 0.72–1.00 and specificity is 0.44–0.77 [47].

*Mood and Anxiety Symptom Questionnaire (MASQ)* [48]. The MASQ is a self-report questionnaire to assess the severity of symptoms of anxiety and depression. It is based on the tripartite model of anxiety and depression symptoms, which can be separated into three groups: global discomfort (anxiety and depression), anhedonia (specific for depression) and physiological hyperarousal (specific for anxiety). The questionnaire consists of 90 items, with an answering scale from 1 to 5 (“not” to “very much”). The scores of the subscales are measured by summating the scores of the items of the subscales. The subscales have sufficient discriminant validity, especially the depression scales [49–51]. The subscales seem to have sufficient internal consistency [48].

*EuroQoL five dimensions questionnaire (EQ-5D*) [52]. The EQ-5D aims to measure health-related quality of life. The EQ-5D is a short questionnaire that consists of five questions with three answer levels, reflecting “no problem”, “some problem” and “extreme problem” in relation to specific dimensions (i.e., mobility, self-care, usual activity, pain and mood). In addition the EQ-5D also includes a Visual Analog Scale (VAS) to value the respondent’s health state, labeled from “best imaginable health” (100) to “worst imaginable health” (0). The EQ-5D can be used to assess sociodemographic differences in health status. Research provides support for the validity of the EQ-5D as a measure for health status [53].

*Short Form Health Survey (SF-36)* [54]*.* We will use the SF-36 to assess health-related quality of life and health status. The SF-36 was developed for a wide range of chronic diseases [54]. It is a multidimensional instrument, with 36 questions to measure eight dimensions: physical functioning, social functioning, role limitations (physical and emotional), mental health, vitality, pain, general health perception and health change. The scores per dimension will be transformed to a scale from 0 to 100 and a higher score denotes a better health status. The Dutch translation has good reliability (Cronbach’s alpha coefficients above .70) and validity [55].

*Trimbos/iMTA Questionnaire for Costs associated with Psychiatric Illness (TiC-P)*, *including the Short Form – Health and Labour Questionnaire (SF-HLQ)* [56]. The Tic-P is a validated tool commonly applied in economic evaluations of treatments in mental health care. The TiC-P is a paper and pencil self-report questionnaire that consists of two parts. The first part obtains information about the volume of health care consumption (direct costs) and the production losses relative to the health problem in question (indirect costs), and some general questions. The second part of the TiC-P, which measures the indirect costs, is the SF-HLQ. The SF-HLQ, an abbreviated version of the HLQ, is a generic and validated measurement instrument to collect data on productivity losses related to health problems in individuals with paid or unpaid work [56]. By multiplying the volumes by the cost prices, it is possible to calculate the costs [57].

#### Putative predictors/mediators

*The Rosenberg Self-Esteem Scale (RSE).* The RSE is a widely-used 10-item Likert scale to measure self-esteem. Items are answered on a 4-point scale – from “strongly agree” to “strongly disagree” – measuring positive and negative feelings towards the self [58]. The Dutch version of the RSE is found to be a one-dimensional scale with high internal consistency (Cronbach’s alpha of 0.89) and congruent validity [59].

*Implicit Association Test Self-Esteem (IAT)* [60]. The IAT will be used to assess implicit self-esteem. The IAT is a computer-administered task, which measures the automatic associations between concepts. The IAT is based on a double discrimination task in which participants are asked to assign single stimuli as fast as possible to a given pair of target categories. The internal consistency has an average score of 0.70 [60].

*Frost Multidimensional Perfectionism Scale (F-MPS)* [61]. We will use the F-MPS to assess perfectionism. The scale contains 35 questions with a 5-point Likert scale from “strongly disagree” to “strongly agree.” When the scale was developed it measured six subscales of perfectionism. It is regarded as internally consistent, reliable over time and displays sound concurrent validity [61, 62]. However, in practical applications, the six-factor structure appeared to be unstable and an alternate four-factor structure was proposed by several others [63, 64].

*Inventory of Interpersonal Problems (IIP-32)* [65]. The IIP is a self-report questionnaire that measures the interpersonal problems that people experience. The instrument was first developed as a 127-item questionnaire on the basis of a list of common interpersonal difficulties raised by persons seeking psychotherapy. The 64-item version was created by Alden et al. [66] specifically to provide a circumplex measure (originally called the IIP-C). For this research we will use the shorter 32-item version (IIP-32), which was developed with the aim of providing a more rapid assessment with a good reliability and validity [67]. All items are rated on a 5-point Likert scale ranging from 0 (“not at all”) to 4 (“extremely”). The questionnaire has good internal consistency, the coefficient alpha for the scales of the IIP-32 are above 0.70 [65].

### Sample size

In order to detect an absolute difference in recovery rate from ED of 25% (CBT-E: 50% versus TAU: 25%), a sample size of 66 patients per treatment condition is required to provide 80% power at two-sided *p* < 0.05 (intention-to-treat analysis). This means that at least 132 patients are needed for this study.

### Randomization, treatment allocation and blinding

Randomization takes place after screening of the inclusion/exclusion criteria and signing of informed consent. The research assistant will randomly assign the participating patients to CBT-E or TAU, stratified by center and type of ED (AN, BN, BED, OSFED). Within each of the twelve strata, a research assistant will randomize participants using a permuted block design. Given the nature of the psychological treatment neither the therapists nor participants can be blinded for the delivered treatment.

### Data management and storage

All study-related data and other study material will be stored securely at the study site (PsyQ The Hague). Participant information and study data will be kept in locked cabinets in areas with limited public access. After obtaining informed consent, participants will be allocated a unique code. The file that links participants to their codes is stored on a secure server hosted by PsyQ and is only accessible by the researcher and research assistant. Any study material concerning participant information will not be released outside the study without written permission from the participant. Online questionnaires will be collected using an authorized SurveyMonkey account and downloaded and added to the database. The SurveyMonkey security and privacy statements for Internet security and handling personal information and data can be found at, respectively, https://www.surveymonkey.com/mp/policy/security/ and https://www.surveymonkey.com/mp/policy/privacy-policy/.

Data collected on paper (SCID-I), will be manually entered into a database. Data collected by the IAT computer task will be transcripted and added to the database. Data integrity will be enforced through several ways, including valid values, range checks and consistency checks. The master database will be held on a secure server hosted by PsyQ, only accessible for authorized personnel involved in the trial. All obtained data and administrative forms (e.g., informed consent) will be stored in accordance with the data storage protocol for 15 years.

### Statistical analysis

All participants who are randomized will be included in the comparison and analyzed according to their randomized allocation (intent-to-treat analysis). Wherever possible, we will continue to collect follow-up data from participants after any dropout from treatment or from the study in order to keep the dataset as complete as possible. In addition, baseline differences in study completers and dropouts will be analyzed with *t* tests for independent samples or chi-square analyses if appropriate. Moreover, we will perform a per-protocol analysis by including only those participants who completed at least 70% of the scheduled therapy sessions. All analyses will be carried out using SPSS 23 [68].

#### Primary study parameter(s)

To test the hypothesis that CBT-E is more effective than TAU, post-treatment differences in recovery rate (based on SCID-I diagnosis) between conditions will be analyzed with chi-square analysis. Using logistic regression analysis with recovery at post treatment as outcome and treatment condition and baseline EDE-Q scores as predictors, whether differences in recovery rate between conditions are independent of severity of ED pathology at pre treatment will also be investigated. Moreover, the course of scores from pre, mid and post treatment to follow-ups I and II on the EDE-Q will be analyzed with multilevel analysis (MLA). MLA is especially suitable to analyze repeated measures data because it takes into account the dependencies among observations nested within individuals. Another advantage of this methodology is its ability to handle missing data, a problem often occurring in longitudinal research [69]. The data have a three-level hierarchical (multilevel) structure: repeated measures at the first level, individuals at the second level and treatment at the third level. Besides main effects for treatment and time, whether groups differ in their course of EDE-Q scores will be investigated by including a treatment × time interaction term. Differences between treatment centers will be investigated likewise.

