## Methods/design

### Design

We will execute a multicenter randomized controlled trial (RCT) with two equal-sized parallel groups at three specialized ED treatment centers from three regions in The Netherlands. Participants will be randomized into two groups (CBT-E versus TAU) stratified by ED center and type of ED. Measurements will take place at pretreatment, 6 weeks, 20 weeks, 40 weeks and 80 weeks, resulting in a 2 (group) × 5 (time) repeated measures factorial design. For an overview of the proposed flow of participants, see Fig. 1. The present study protocol was written in accordance with the Standard Protocol Items: Recommendations for Interventional Trials (SPIRIT) [28]; copies of the SPIRIT Checklist and figure have been included in Additional files 1 and 2.

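### The primary recovery test leaves out the centre and ED-type factors that define the randomisation strata, and the EDE-Q multilevel analysis stands under the primary heading

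*Protocol article*

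**What the plan says.** The Design section has participants randomised "stratified by ED center and type of ED". The section on randomization, treatment allocation and blinding gives four types (AN, BN, BED, OSFED) at three centres, hence twelve strata, each with permuted blocks.

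The section *Primary study parameter(s)* then sets out three analyses:

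1. A test of the main hypothesis, the superiority of CBT-E, on the primary outcome: "post-treatment differences in recovery rate (based on SCID-I diagnosis) between conditions will be analyzed with chi-square analysis".
2. A logistic regression of post-treatment recovery on treatment and baseline EDE-Q, by which "whether differences in recovery rate between conditions are independent of severity of ED pathology at pre treatment will also be investigated".
3. A multilevel analysis of "the course of scores from pre, mid and post treatment to follow-ups I and II on the EDE-Q".

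The one sentence on centre differences follows the multilevel model and refers back to it. ED type enters no planned analysis.

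On the status of the outcomes, the Objectives section defines the primary aim as "a higher percentage of recovery from EDs compared to TAU". The abstract also names recovery as the primary outcome and ED psychopathology as secondary, and the Measurements section lists the EDE-Q under "Secondary study parameters".

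**The concern.** Stratified blocks force the arms to be nearly balanced on centre and ED type. If those factors predict recovery, part of the outcome variance can no longer contribute to the difference between arms. An unadjusted chi-square still counts that part in its standard error, so it rejects less often than 5% under the null and loses power. Baseline EDE-Q is different: it is not a stratification factor, so leaving it out does not make the test conservative, but any precision it could supply is lost.

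The protocol gives some reason to think the factors matter. The Background says that TAU differs by ED category, and the description of TAU says that its intensity depends on site policy. It gives no figures on prognosis. The Sample size section carries no allowance for dropout, so precision available from variables already collected is worth having.

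The second matter is placement. An outcome that is secondary in the abstract and in the Measurements section is analysed under the primary heading, and the next section speaks of the secondary outcome measures as if the EDE-Q were not among them.

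**Working it through.** **Step 1: the plan's own figure.** Inputs from the Sample size section: recovery 50% (CBT-E) versus 25% (TAU), two-sided 5%, 80% power, 66 per arm. Mean proportion 0.375, difference d = 0.25.

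- Without continuity correction: n = [1.960·√(2·0.375·0.625) + 0.8416·√(0.5·0.5 + 0.25·0.75)]² / 0.25² = (1.3419 + 0.5567)² / 0.0625 = 57.7, so 58 per arm.
- With continuity correction: (n/4)·[1 + √(1 + 4/(n·d))]² = (57.67/4)·[1 + √(1 + 4/14.42)]² = 14.42·(2.1302)² = 65.4, so **66 per arm**, as stated.
- Power of the uncorrected chi-square at 66 per arm: z = (0.25·√66 − 1.3419)/0.6614 = 1.042, which gives 85.1%.

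The stated size therefore fits the stated test.

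**Step 2: effect of leaving out the strata.** Trials of 132 patients were simulated, 4,000 per scenario. From the protocol: centres of 60, 36 and 36, four ED types, permuted blocks within twelve strata, and 25% versus 50% recovery. Assumed, because the protocol gives no figure: ED mix of 10/35/25/30% (AN/BN/BED/OSFED), block size 4, and these prognostic effects on the log-odds scale:

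- centre: −s, 0, +s
- ED type: −1.0s, −0.3s, +0.9s, +0.4s
- EDE-Q: b per SD

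with (s, b) = (0, 0), (0.4, 0.4), (0.7, 0.7) and (1.0, 0.8). The null was run at common recovery rates of 25% and 37.5%. MH is Mantel-Haenszel over the twelve strata. The full logistic model has treatment, centre, ED type and EDE-Q, with a Wald test and no penalty.

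| Prognostic strength | Type I error, % (25% / 37.5%): chi-square | MH | Full logistic | Power, %: chi-square | Planned logistic (treatment + EDE-Q) | MH | Full logistic |
|---|---|---|---|---|---|---|---|
| None | 5.4 / 4.9 | 5.2 / 4.8 | 5.6 / 5.2 | 86.4 | 85.9 | 86.1 | 86.5 |
| Weak | 5.0 / 4.7 | 5.2 / 5.1 | 5.5 / 5.4 | 85.3 | 85.8 | 85.5 | 87.0 |
| Moderate | 4.2 / 4.2 | 5.0 / 5.2 | 5.5 / 5.5 | 86.4 | 88.9 | 87.9 | 91.4 |
| Strong | 3.4 / 3.6 | 4.8 / 5.3 | 5.1 / 5.5 | 87.2 | 89.4 | 90.1 | 93.0 |

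Monte Carlo standard errors are about 0.3 points for type I error and 0.4 to 0.6 for power.

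- Gain over the chi-square from strata alone (MH): −0.3, +0.2, +1.5 and +2.9 points, or about 0 to 3.
- Gain from strata plus EDE-Q (full logistic): +0.1, +1.7, +5.0 and +5.8 points, or about 0 to 6. A little of this may reflect the full model's slightly high type I error.

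The protocol does not say whether a continuity correction will be used. With it, simulated chi-square power is 80.7% to 82.5% and type I error 2.1% to 3.4%.

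**Step 3: can the data carry the adjusted model?** Expected recoveries are 66·0.50 + 66·0.25 = 49.5. The model has seven terms besides the intercept (treatment 1, centre 2, ED type 3, EDE-Q 1), or about 7 recoveries per term. That is workable with care. Twelve separate stratum terms would not be, since strata average only 132/12 = 11 patients.

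**The case against.** The strongest reply is that nothing here is invalid. The chi-square holds its level, matches the power calculation and exceeds the planned 80%. The benefit of adjustment depends on prognostic effects for which the protocol has no data, and is close to nil if they are weak. Baseline EDE-Q is not ignored altogether, since the planned logistic regression uses it. Centre is considered too, though only with the EDE-Q multilevel model. The Discussion also says that the sample is too small for subgroup analyses. All of this stands, except that the last point concerns differential effects by diagnosis; main-effect adjustment for ED type makes no such demand. Nor is this detail left to an unseen analysis plan: the article itself names the test and the covariates.

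Three stronger readings are tempting, and the protocol does not support them:

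- A reader might infer that the plan leaves open which of the three analyses decides. In fact the hypothesis is tied to the chi-square, the other two are introduced as additions, and the objective and sample size concern recovery alone.
- A reader might then infer an inflated family-wise error, for instance 1 − 0.95² = 9.8% for recovery and EDE-Q. That needs two co-equal, independent tests. The protocol makes the EDE-Q secondary, and both outcomes measure ED pathology.
- A reader might infer that a treatment-by-severity interaction is owed. Asking whether the difference is independent of baseline severity is ordinarily a question of covariate adjustment, which the planned model answers.

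**Conclusion.** The point holds as one of efficiency and consistency. Neither recovery analysis reflects the stratified design. The chi-square is valid and adequately powered, but it becomes conservative to the extent that centre and ED type predict recovery: type I error falls from about 5% to 3.4% across the scenarios assumed. The power forgone is about 0 to 3 points for the strata and 0 to 6 with EDE-Q added. These ranges rest on the assumed ED mix, block size and prognostic strengths. There is no added false-positive risk and no error in the sample size. Separately, the EDE-Q multilevel analysis is under the wrong heading, at odds with the abstract and the Measurements section. The change is worth making because it costs little; the trial does not fail without it.

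**What to change.** Name one primary analysis of week-20 SCID-I recovery at two-sided 5%: logistic regression on treatment, centre and ED type (as main effects) and baseline EDE-Q, with a safeguard for sparse categories such as a Firth penalty. Mantel-Haenszel stratified by the randomisation factors is a simpler alternative, though it leaves out the EDE-Q. Report a standardised risk difference with 95% CI beside the odds ratio, so that the result stays on the scale of the 25-point difference used for planning. Keep the chi-square as supportive, and say whether it is continuity-corrected. Move the EDE-Q multilevel analysis to the secondary section.

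The cost is wording, settled before outcomes are compared by arm. The odds ratio becomes conditional on the covariates, and small categories need care. All the covariates are already collected, and neither sample size nor data collection changes.
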